## **SECTION B: SMOKING EXPERIENCES**

First, I want to ask you a little about your history with smoking tobacco. Please, can you take a moment to think back to when you began smoking.

### **1. How old were you when you started smoking regularly?**

*Prompt (if needed):*

If participant cannot give an exact age, a ballpark number or some other indicator (e.g., a year in school; before/after a significant life event) works as well

### **2. What influenced you to begin smoking?**

*Prompt (if needed):*

- *What led you to start smoking?*
- *Did you feel pressured by anyone to smoke?*

Now thinking about over the last week

### **3. Tell me about when and how much you smoke.**

*Prompt (if needed):*

- *What time of day?*
- *How many times on a typical day?*

### **4. Does having HIV impact your smoking behaviors?**

*Prompt (if needed):*

- *Do you smoke more, less, or the same amount?*
- *Why do you think that is?*

### **5. What makes you smoke?**

*Prompt (if needed):*

- *Pleasure, alleviate boredom*
- *Stress, manage depression or anxiety, manage anger*

- *Avoid withdrawal symptoms*
- *Manage pain or medications (e.g., make them work better, remove bad taste)*
- *Part of a social activity*
- *Weight management*
- *Need to (addicted to it); too hard to quit*
- *Avoid use of harder drugs or alcohol*
- *Helps with energy levels or concentration*
- *Not worried about health*

**6. Are these things that make you smoke now different from the things that made you smoke when you first started?**

*Prompt (if needed):*

- *Why do you think that is?*

Now, when you think about these reasons for why you smoke [*note a few or all of them*]

**7. Which of these reasons for smoking make it most difficult to quit?**

### **SECTION C: SMOKING CESSATION**

Thank you for everything you have shared so far. I want to ask you a bit more about your thoughts and experiences with quitting smoking.

**1. Have you recently tried to quit smoking? IF YES,**

**a. What reasons, recently, made you want to quit smoking?**

**2. Had you tried to quit smoking in the past? (Yes or No)**

*IF YES, were you successful?*

*IF YES*

- a. What prompted you to quit smoking then?
- b. What helped you the most with this?
- c. Why do you think you weren't able to successfully quit?

*IF NO*

- a. Why do you think you have not tried to quit in the past?
- b. What is different about your recent circumstances that you have tried to quit recently?

**3. What characteristics or resources could help you quit next time?**

*Prompt (if needed):*

- *Aspects of your personality (e.g., determined, resilient)?*
- *Aspects of your situation (e.g., family or friends who motivate you)?*
- *How do these characteristics help you?*

**4. Is there anything else you think, had you had access to, would have helped you stop smoking?**

**SECTION D: EXPERIENCES WITH SBIRT**

I really appreciate you sharing all of that with me. Now, we are in the last section of my prepared questions, and they focus on your experiences with the support you received related to smoking cessation and varenicline.

If you could please take a moment to think back to when you were referred to SBIRT. You were screened to participate and then worked with a health worker who referred you to receive the varenicline. Specifically, your health worker discussed quitting smoking with you.

**1. How did that conversation go?**

- a. Did you feel the health worker understood your situation and perspectives well?
- b. Did the health worker listen to and address your concerns and questions?
- c. Did you feel comfortable saying "no" to them?
- d. Did you feel like you had a good understanding of what you were agreeing to do?

2. Have you had additional check-ins or conversations with your health worker about managing your smoking?
  - a. What aspects of these interactions were helpful?
3. Is there anything that your health worker could have done differently to make this experience better?

Great, this has been really helpful.

Now, I want you to think about your experiences with varenicline.

4. Were you prescribed a drug called Varenicline to take?

*IF NO, Go to the closing section. IF YES,*

5. What was it like for you taking varenicline?

*Prompts (if needed):*

- Did you experience side effects? What were they like?

6. Is there anything that would have helped you better prepare for integrating varenicline into your routine?

7. Do you have any other recommendations for improving this intervention to better support smoking cessation?

*Prompts (if needed):*

- Anything your health worker could have done differently?
- Anything the prescribing nurse could have done differently?
- Anything other members of your support community could have done?

## **SECTION E: CLOSING**

I really appreciate all of your answers and everything you have shared with me today.

- 1. Is there anything else that you feel we should have talked about regarding your experiences with trying to quit smoking?**
  
- 2. Is there anything else you'd like to share about your experiences with the SBIRT intervention or varenicline?**

Those are all the prepared questions I have. Thank you for taking the time to talk with me today. As a reminder, all of your responses will always be kept confidential and will never be linked with your name or other identifying information.

Do you have any questions for me at this time? If anything comes up in the future, your consent form has contact information listed on it. Please feel free to contact us.

[after responding to any questions or concerns] **STOP RECORDING**

## Appendix E2: SSIs for participants who quit and then resumed smoking

### BSMART Participant Interview Guide

#### Participants Who Quit then Resumed Smoking

**Note to Interviewer:**

**Text in red refers to important directions for you.**

#### SECTION A: INTRODUCTION

Thank you for taking the time to talk with me today. My name is \_\_\_\_\_ and I am part of a team doing research on how we can help people quit smoking, especially when they encounter challenges when trying to do so.

Our conversation today will be quite informal, so please feel free to share anything you think would be important or helpful for us to know about your experiences with smoking and trying to quit.

I have a list of prepared questions that I will ask you. Sometimes I may ask you to expand or clarify your responses, I do this to make sure I fully understand. Other times I may ask that we move onto the next topic so that I can respect your time and ensure we can cover everything we need to get through.

You may or may not remember that I will be audio recording this interview. The reason for that is so that I can focus on what you are saying without trying to write it all down. No one will hear the recording except for people working on the project and we will remove any identifying information from the transcript of the interview. In reports from this project, we will never identify you as a participant or provide any information that allows other people to figure out you took part.

As a reminder, your participation in this interview is completely voluntary. If there are any questions you'd rather not answer, that is fine – just let me know. And, if at any point, you need a break, you can let me know that too. We are interested in your honest thoughts and experiences so there are no “right” or “wrong” answers to my questions.

Do you have any questions before we begin the interview?

[after responding to any questions or concerns] **START RECORDING**

Let's get started!

## **SECTION B: SMOKING EXPERIENCES**

First, I want to ask you a little about your history with smoking tobacco. Please, can you take a moment to think back to when you began smoking.

### **8. How old were you when you started smoking regularly?**

*Prompt (if needed):*

*If participant cannot give an exact age, a ballpark number or some other indicator (e.g., a year in school; before/after a significant life event) works as well.*

### **9. What influenced you to begin smoking?**

*Prompt (if needed):*

- *What led you to start smoking?*
- *Did you feel pressured by anyone to smoke?*

Now thinking about over the last week

### **10. Tell me about when and how much you used to smoke before you last stopped.**

*Prompt (if needed):*

- *What time of day?*
- *How many times on a typical day?*

### **11. Does having HIV impact your smoking behaviors?**

*Prompt (if needed):*

- *Do you smoke more, less, or the same amount?*
- *Why do you think that is?*

### **12. What makes you smoke lately?**

*Prompt (if needed):*

- *Pleasure, alleviate boredom*
- *Stress, manage depression or anxiety, manage anger*
- *Avoid withdrawal symptoms*
- *Manage pain or medications (e.g., make them work better, remove bad taste)*
- *Part of a social activity*
- *Weight management*
- *Need to (addicted to it); too hard to quit*
- *Avoid use of harder drugs or alcohol*
- *Helps with energy levels or concentration*
- *Not worried about health*

**13. Are these things that make you smoke now, different from the things that made you smoke when you first started?**

*Prompt (if needed):*

- *Why do you think that is?*

Now, when you think about these reasons for why you smoke [*note a few or all of them*]

**14. Which of these reasons for smoking made it most difficult for you to stay abstinent?**

### **SECTION C: SMOKING CESSATION**

Thank you for everything you have shared so far. I want to ask you a bit more about your thoughts and experiences with quitting smoking.

**5. What reasons, recently, made you want to quit smoking?**

**6. Had you tried to quit smoking in the past?**

*IF YES*

- What prompted you to quit smoking then?
- What helped you the most with this?

**Now, thinking about your most recent attempt to quit smoking...**

- 7. What was different about your recent circumstances that made you try to quit recently?**
- 8. Why do you think you weren't able to stay abstinent this time?**
- 9. How ready did you feel to quit?**
- 10. When you decided to stop smoking again this most recent time, how confident were you that you could succeed?**
- 11. What characteristics or resources could help you stay abstinent next time?**

*Prompt (if needed):*

- *Aspects of your personality (e.g., determined, resilient)?*
- *Aspects of your situation (e.g., family or friends who motivate you)?*
- *How do these characteristics help you?*

- 12. Are there other things, beside your personal characteristics, that helped you resist smoking as long as you did?**

*Prompt (if needed):*

- Support from others (e.g., care team, family, friends); Medications
- Why do you think that was helpful?

- 13. On the other hand, what challenges did you experience with staying abstinent?**

9a. What do you think would help you to overcome these challenges in the future?

**14. Is there anything else you think, had you had access to, would have helped you stay abstinent for longer?**

#### **SECTION D: EXPERIENCES WITH SBIRT**

I really appreciate you sharing all of that with me. Now, we are in the last section of my prepared questions, and they focus on your experiences with the support you received related to smoking cessation and varenicline.

If you could please take a moment to think back to when you referred to SBIRT. You were screened to participate and then worked with a health worker who referred you to receive the varenicline. Specifically, your health worker discussed quitting smoking with you.

**8. How did that conversation go?**

- a. Did you feel the health worker understood your situation and perspectives well?
- b. Did the health worker listen to and address your concerns and questions?
- c. Did you feel comfortable saying “no” to them?
- d. Did you feel like you had a good understanding of what you were agreeing to do?

**9. Have you had additional check-ins or conversations with your health worker about managing your smoking?**

- a. What aspects of these interactions were helpful?

**10. Is there anything that your health worker could have done differently to make this experience better?**

Great, this has been really helpful. Now, I want you to think about your experiences with varenicline.

**11. Were you prescribed a drug called Varenicline to take?**

*IF NO, Go to the closing section. IF YES,*

**12. What was it like for you taking varenicline?**

*Prompts (if needed):*

- *Did you experience side effects?*
- *What were they like?*

**13. Is there anything that would have helped you better prepare for integrating varenicline into your routine?**

**14. Do you have any other recommendations for improving this intervention to better support smoking cessation?**

*Prompts (if needed):*

- *Anything your health worker could have done differently?*
- *Anything the prescribing nurse could have done differently?*
- *Anything other members of your support community could have done?*

### **SECTION E: CLOSING**

I really appreciate all of your answers and everything you have shared with me today.

**3. Is there anything else that you feel we should have talked about regarding your experiences with trying to quit smoking?**

**4. Is there anything else you'd like to share about your experiences with the SBIRT intervention or varenicline?**

Those are all the prepared questions I have. Thank you for taking the time to talk with me today. As a reminder, all of your responses will always be kept confidential and will never be linked with your name or other identifying information.

Do you have any questions for me at this time? If anything comes up in the future, your consent form has contact information listed on it. Please feel free to contact us.

[after responding to any questions or concerns] **STOP RECORDING**

## BSMART Participant Interview Guide

### Participants Who are Currently not Smoking

**Note to Interviewer:**

**Text in red refers to important directions for you.**

#### SECTION A: INTRODUCTION

Thank you for taking the time to talk with me today. My name is \_\_\_\_\_ and I am part of a team doing research on how we can help people quit smoking, especially when they encounter challenges when trying to do so.

Our conversation today will be quite informal, so please feel free to share anything you think would be important or helpful for us to know about your experiences with smoking and trying to quit. I have a list of prepared questions that I will ask you. Sometimes I may ask you to expand or clarify your responses, I do this to make sure I fully understand. Other times I may ask that we move onto the next topic so that I can respect your time and ensure we can cover everything we need to get through.

You may or may not remember that I will be audio recording this interview. The reason for that is so that I can focus on what you are saying without trying to write it all down. No one will hear the recording except for people working on the project and we will remove any identifying information from the transcript of the interview. In reports from this project, we will never identify you as a participant or provide any information that allows other people to figure out you took part.

As a reminder, your participation in this interview is completely voluntary. If there are any questions you'd rather not answer, that is fine – just let me know. And, if at any point, you need a break, you can let me know that too. We are interested in your honest thoughts and experiences so there are no “right” or “wrong” answers to my questions.

Do you have any questions before we begin the interview?

[after responding to any questions or concerns] **START RECORDING**

Let's get started!

## **SECTION B: SMOKING EXPERIENCES**

First, I want to ask you a little about your history with smoking tobacco. Please, can you take a moment to think back to when you began smoking.

### **15. How old were you when you started smoking regularly?**

*Prompt (if needed):*

*If participant cannot give an exact age, a ballpark number or some other indicator (e.g., a year in school; before/after a significant life event) works as well*

### **16. What influenced you to begin smoking?**

*Prompt (if needed):*

- *What led you to start smoking?*
- *Did you feel pressured by anyone to smoke?*

Now thinking about over the last week

### **17. Tell me about when and how much you used to smoke before you last stopped?**

*Prompt (if needed):*

- *What time of day?*
- *How many times on a typical day?*

### **18. When you smoked, did having HIV impact your smoking behaviors?**

*Prompt (if needed):*

- *Do you smoke more, less, or the same amount?*
- *Why do you think that is?*

**19. What made you smoke (before you stopped)?**

*Prompt (if needed):*

- *Pleasure, alleviate boredom*
- *Stress, manage depression or anxiety, manage anger*
- *Avoid withdrawal symptoms*
- *Manage pain or medications (e.g., make them work better, remove bad taste)*
- *Part of a social activity*
- *Weight management*
- *Need to (addicted to it); too hard to quit*
- *Avoid use of harder drugs or alcohol*
- *Helps with energy levels or concentration*
- *Not worried about health*

**SECTION C: SMOKING CESSATION**

Thank you for everything you have shared so far. I want to ask you a bit more about your thoughts and experiences with quitting smoking.

**15. What reasons, recently, made you want to quit smoking?**

**16. What helped you the most with this?**

Now, thinking about your most recent attempt to quit smoking...

**17. How ready did you feel to quit?**

**18. When you decided to stop smoking again this most recent time, how confident were you that you could succeed?**

- a. How capable did you feel?
- b. How capable do you feel now?

**19. What characteristics or resources do you have that you think helped you with quitting?**

*Prompt (if needed):*

- *Aspects of your personality (e.g., determined, resilient)?*
- *Aspects of your situation (e.g., family or friends who motivate you)?*

- *How do these characteristics help you?*

**20. Are there other things, beside your personal characteristics, that helped you quit and stay off smoking as long as you have?**

*Prompt (if needed):*

- *Support from others (e.g., care team, family, friends); Medications*
- *Why do you think that was helpful?*

**21. On the other hand, what challenges did you experience with quitting?**

- How did you overcome these challenges?

**22. Is there anything else you think, had you had access to, would have helped you stop smoking sooner? Or would have made it easier for you to quit?**

#### **SECTION D: EXPERIENCES WITH SBIRT**

I really appreciate you sharing all of that with me. Now, we are in the last section of my prepared questions, and they focus on your experiences with the support you received related to smoking cessation and varenicline.

If you could please take a moment to think back to when you referred to SBIRT. You were screened to participate and then worked with a health worker who referred you to receive the varenicline. Specifically, your health worker discussed quitting smoking with you.

**15. How did that conversation go?**

- Did you feel the health worker understood your situation and perspectives well?
- Did the health worker listen to and address your concerns and questions?
- Did you feel comfortable saying “no” to them?
- Did you feel like you had a good understanding of what you were agreeing to do?

**16. Have you had additional check-ins or conversations with your health worker about managing your smoking?**

- a. What aspects of these interactions were helpful?

**17. Is there anything that your health worker could have done differently to make this experience better?**

Great, this has been really helpful. Now, I want you to think about your experiences with varenicline.

**18. Were you prescribed a drug called Varenicline to take?**

*IF NO, Go to the closing section. IF YES,*

**19. What was it like for you taking varenicline?**

*Prompts (if needed):*

- Did you experience side effects?
- What were they like?

**20. Is there anything that would have helped you better prepare for integrating varenicline into your routine?**

**21. Do you have any other recommendations for improving this intervention to better support smoking cessation?**

*Prompts (if needed):*

- Anything your health worker could have done differently?
- Anything the prescribing nurse could have done differently?
- Anything other members of your support community could have done?

## **SECTION E: CLOSING**

I really appreciate all of your answers and everything you have shared with me today.

5. **Is there anything else that you feel we should have talked about regarding your experiences with quitting smoking?**
  
6. **Is there anything else you'd like to share about your experiences with the SBIRT intervention or varenicline?**

Those are all the prepared questions I have. Thank you for taking the time to talk with me today. As a reminder, all of your responses will always be kept confidential and will never be linked with your name or other identifying information.

Do you have any questions for me at this time? If anything comes up in the future, your consent form has contact information listed on it. Please feel free to contact us.

[after responding to any questions or concerns] **STOP RECORDING**

## Appendix F: Activity Log:

Date: \_\_\_\_\_

Lay case manager ID: \_\_\_\_\_

Number of patients invited to enroll \_\_\_\_\_ Number enrolled \_\_\_\_\_

|               | Duration of counselling | Outcome of counselling (agreed to participate; declined) | Referred to NPT (N/A; YES; NO) | Outcome of referral | Challenges |
|---------------|--------------------------------|-----------------------------------------------------------------|---------------------------------------|----------------------------|-------------------|
| Participant 1 |                                |                                                                 |                                       |                            |                   |
| Participant 2 |                                |                                                                 |                                       |                            |                   |
| Participant 3 |                                |                                                                 |                                       |                            |                   |
| Participant 4 |                                |                                                                 |                                       |                            |                   |

The logs will collect information about implementation activities, intent, duration, and individuals involved.

[figure not shown]

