**Workflow Processes:** We will review how to integrate SBIRT into the care team. For example, we will have a LHW case manager in place at the outpatient clinics whose scope will be adapted to meet with the new and existing patients before the end of the clinic visit to introduce the study and conduct the 5”A”s. Other adaptations will include: 1) developing and piloting the new clinical workflow between LHW case manager and nurse prescriber/dispenser; 2) training the care team in implementing the new workflow; and 3) using monthly activity logs to track implementation strategies such as actions, methods, events, or efforts to promote adoption and implementation of SBIRT components.

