### 2. Measures to assess the Adoption and Implementation of SBIRT

- Activity Logs: During the implementation period, implementation leaders and care teams will be sent a monthly email requesting that they complete an activity log, which will take 15–30 minutes to complete depending on the number of activities to report. The logs will collect information about implementation activities, intent, duration, and individuals involved. We will ask them to take an inclusive approach and include any activities they believe are related to implementation. We will also add a hypothetical example to the instructions and share a list of discrete implementation strategies. Each month, the research team will invest up to two hours to collect and combine the logs then follow-up with implementation leaders at sites to address their questions.
- Scripts from Focus Group discussions with LHWs
- Responses from SSIs
- SBIRT checklists

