#### Process Variables

| Tool                                              | Data collector                        | Timing                                 |
|---------------------------------------------------|---------------------------------------|----------------------------------------|
| Activity Logs                                     | Research Assistant/ LHW               | Monthly during intervention
phase   |
| 40-item Program Sustainability
Assessment Tool | Investigators/ Research
Assistants | Intervention and
maintenance phases |

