Quantitative measure of implementation success. Implementation effectiveness will be assessed by measuring the extent of integration of BSMART into the clinical setting within participating facilities. Therefore, we will focus on **Adoption** which will be analyzed monthly and for the 12 months of implementation as the number of clinic days per month LHW case managers delivered SBIRT divided by the number of operating clinic days per month. **Implementation with fidelity** will be analyzed monthly and for the 12 months of implementation period as the number of SBIRT provided with repeated intervention over time by LHW case managers to PLWH who smoked divided by the number of PLWH who are eligible for the program. Pearson's correlation will be used to assess the strength of correlation between qualitatively derived construct ratings from qualitative interviews and activity logs, and implementation effectiveness across facilities.

### Statistical Analysis for Study Objective 3

RE-AIM measures will be re-assessed at 24 months after BSMART implementation to provide a standardized evaluation approach to foster understanding of whether the impact and implementation delivery are maintained and to shed light on where sustainability issues arise e.g. which clinic and population the implementation is not reaching. Trends in the outcomes of clinical effectiveness (collected and analyzed in Study Objective 1) and implementation effectiveness (collected and analyzed in Study Objective 2) will be compared between the implementation period and the maintenance period using chi-square test.

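### The Appendix F activity log does not collect the implementation-strategy data that Objective 2 codes and rates, and it shows raters counselling and referral activity related to the outcome

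*Protocol*

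**What the plan says.** The section on site integration and training for SBIRT introduces the log as a tracking tool: "using monthly activity logs to track implementation strategies such as actions, methods, events, or efforts to promote adoption and implementation of SBIRT components". The section on measures of adoption and implementation says that "implementation leaders and care teams will be sent a monthly email requesting that they complete an activity log", that the team will "share a list of discrete implementation strategies" to help respondents, and that "The logs will collect information about implementation activities, intent, duration, and individuals involved". It allows 15 to 30 minutes a month for this.

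The Process Variables table also gives monthly timing but names the data collector as "Research Assistant/ LHW".

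The Appendix F form is headed by a date, a lay case manager ID, "Number of patients invited to enroll" and the number enrolled. Each row is one participant, with five columns: duration of counselling, "Outcome of counselling (agreed to participate; declined", whether referred, outcome of referral, and challenges. The sentence printed under the table repeats the content definition from the measures section.

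The statistical analysis for Study Objective 2 codes interviews and logs to CFIR constructs. Two analysts, blinded to implementation effectiveness, rate each code from -2 to +2. Interviews are rated in two rounds and logs monthly. Then "Pearson's correlation will be used to assess the strength of correlation between qualitatively derived construct ratings from qualitative interviews and activity logs, and implementation effectiveness", with the facility as the unit. Implementation effectiveness means adoption (days with SBIRT delivered over operating clinic days) and fidelity (repeated SBIRT provided over eligible patients).

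**The concern.** The log as defined and the log as printed are different instruments. The first describes what staff did to get the programme running, why, for how long and with whom. The second describes what happened to each patient who was approached.

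Two things are at stake. First, strategy data that are not captured month by month cannot be reliably recovered later, so a named input to the Objective 2 analysis would be largely missing. Second, analysts who rate a facility from these forms would be reading its counselling and referral activity, while the outcome set against their ratings is a measure of SBIRT delivery in the same facility. This is a defect of a fixed data-collection form and its stated use, so a later analysis plan could not repair it.

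**Working it through.** The protocol gives no figure to reproduce here. The check compares the fields of the form with the definition of the log, and then with the variables of the analysis.

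**Step 1: defined content against the form.**

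| Item in the definition | In Appendix F |
|---|---|
| Implementation activities | No field |
| Strategy, chosen with the help of the supplied list | No field |
| Intent | No field |
| Duration | Duration of counselling only |
| Individuals involved | In part: case manager ID and participant rows |

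Of the four items in the content sentence (activities, intent, duration, individuals), two are absent and two are partial. The strategy list adds a fifth element, also absent. The form therefore contradicts the sentence under its own table.

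**Step 2: unit of rating.** The analysis needs a rating per facility and period. Appendix F has no facility field, although the screening, demographics and intake smoking forms all have one. It has a date but no reporting month. Facility might be traced through the case manager ID and month through the date, but the form is not laid out as a monthly return.

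**Step 3: respondent.** The measures section names implementation leaders and care teams. The Process Variables table names the research assistant or lay health worker. The form asks for a lay case manager ID. Implementation leaders, the people best placed to report strategies, appear only in the first.

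**Step 4: what can be coded.** Of the five row columns, only *Challenges* asks about barriers. The others record enrolment, counselling and referral. Nothing prompts for a facilitator or a strategy, although the rating scale runs to +2.

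**Step 5: how much rests on the log.** Over the 12-month implementation period at 15 facilities, monthly logs give 12 × 15 = 180 facility-level rating occasions per code. Two interview rounds give 2 × 15 = 30. The log is thus the source of 180/30 = 6 times as many occasions, and the only monthly source of ratings, while adoption and fidelity are also analysed monthly. The protocol does not say how the two sources are weighted, so this shows how often the log is used, not its share of the result.

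**Step 6: overlap with the outcome.** Adoption and fidelity measure SBIRT delivery. Appendix F shows raters, by date and case manager, who was counselled and referred. That is related information, though not the same variable. It works against the stated blinding for the log-derived ratings.

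**The case against.** A reader might infer that the correlation would relate SBIRT delivery to itself. The documents do not support that, for four reasons, all of which stand:

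- The ratings also come from two rounds of interviews, which do not use this form.
- Log data enter as analysts' judgements on CFIR codes from -2 to +2. Nothing says that counts are rated.
- The raters are to be blinded to implementation effectiveness. The form weakens this safeguard but does not remove it.
- The 5A's checklist is named as the document of SBIRT delivery and is listed separately from the logs. Nothing says that adoption or fidelity is computed from Appendix F, and the agreed-or-declined column is closer to enrolment than to either.

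For the same reasons, any figure for an inflated false-positive rate would rest on an assumed artefactual correlation for which the protocol gives no basis. None is offered here.

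It can also be said that one sub-aim of Objective 2 is to inform the development of the logs, so Appendix F might be a starting point. But nothing marks the form as provisional. Finally, an image whose content could not be read follows the form. The contents list puts Appendices F, G and H on pages 163, 164 and 165, and no Appendix G heading appears in the text, so the image is probably the Appendix G tool. A further page of the log cannot be fully excluded.

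**Conclusion.** The mismatch holds. As printed, the Appendix F form cannot supply the implementation-strategy data that the protocol says the log collects and that Objective 2 codes and rates, and three places name different respondents. Little beyond the *Challenges* text would be available for the monthly ratings.

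Circularity is a risk confined to the log-derived part of the correlation. It arises because raters see activity related to the outcome from which they are meant to be blinded. Its size cannot be derived from the protocol.

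The point should be corrected, but it concerns one input to an implementation analysis. The primary abstinence endpoint and its analysis are unaffected. The conclusion assumes that Appendix F is the form to be used and that the unreadable image is not a second page of it.

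**What to change.** Before log collection starts:

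1. Replace the Appendix F table with the fields already promised in the measures section: activity, strategy from the supplied list, intent, duration and individuals involved. Add facility and reporting month.
2. State once who completes the log, and make the measures section, the Process Variables table and Appendix F agree.
3. If the counselling and referral tally is still wanted, keep it as a separate form that is not shown to the analysts who rate CFIR codes.
4. Leave the 5A's checklist as the record of SBIRT delivery. Do not route the tally into adoption or fidelity, which would create a second source for the same numerators.

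The cost is one redesigned form and matching edits to the text. The monthly time already allowed, 15 to 30 minutes, was set for the log as described, so no extra staff time is implied unless the tally is kept as well.
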